## Abstract

**Background:**

Surgery is the gold standard treatment for local advanced disease, while definitive concurrent chemoradiotherapy (DCRT) is recommended for those who are medically unable to tolerate major surgery or medically fit patients who decline surgery. The primary aim of this trial is to compare the outcomes in Chinese patients with oesophageal squamous cell cancer with locally advanced resectable disease who have received either surgery or DCRT.

**Methods/design:**

One hundred ninety-six patients with T1bN + M0 or T2-4aN0-2 M0 oesophageal squamous cell cancer will be randomised to the DCRT group or the surgery group. In the DCRT group, patients will be given intensity-modulated radiation therapy (IMRT) with 50 Gy/25 fractions and basic chemotherapy with 5-fluorouracil regimens. In the surgery group, patients will receive neoadjuvant chemoradiotherapy (NCRT) and standard oesophagectomy. Five years of follow-up will be scheduled for patients. The primary endpoints are 2-year/5-year overall survival; the secondary endpoints are 2-year/5-year progression-free survival, treatment-related adverse events and the patients’ quality of life. The main evaluation methods include oesophagoscopy, endoscopic ultrasonography and biopsy, oesophageal barium meal, computed tomography, positron emission tomography-computed tomography, blood tests and questionnaires.

**Discussion:**

The preponderant oesophageal cancer pathology type is dramatically different in western Caucasian and Asian oesophageal cancer patients: Caucasian patients present with 80% adenocarcinomas, and Asians patients present with 95% squamous cell carcinomas. This phenomenon needs more in-depth studies to elucidate the differences in these populations. Based on the results of this study, we will show whether DCRT will benefit patients more than oesophagectomy. This study will contribute more evidence to the management of oesophageal squamous cell cancer.

**Trial registration:**

ClinicalTrials.gov, NCT02972372. Registered on 26 November 2016.

**Electronic supplementary material:**

The online version of this article (10.1186/s13063-019-3316-5) contains supplementary material, which is available to authorized users.

## Background

Oesophageal cancer (EC) is the eighth most common cancer worldwide and the sixth leading cause of cancer-related death [1]. In 2012, 456,000 EC cases occurred, and 400,000 people died from EC worldwide. It’s remarkable that almost half of them came from China, with 223,000 EC cases and 197,000 death cases in 2012. Both the highest incidence and highest mortality, 379/100,000 and 150/100,000, respectively, were in Henan, China (including Linzhou, Anyang and Huixian cities). Additionally, EC is the fourth most deadly cancer among men in China; it is responsible for 9.8% of all cancer deaths annually [2].

Worldwide, approximately half of these patients present with locally advanced disease [3]. Radical oesophagectomy remains the most popular treatment for this disease, but the long-term survival is still barely satisfactory [4, 5]. The mortality in the perioperative period is approximately 5% at renowned centres. The 5-year survival rate in patients with oesophageal carcinoma treated by surgery alone is just 10–20% [6]. Numerous clinical studies in past decades have used adjuvant or neoadjuvant chemotherapy and radiotherapy as a tool to improve the clinical outcome of surgery [7]. However, the results from prospective randomised trials on neoadjuvant radiotherapy or chemotherapy alone were not satisfactory [8]. There was no survival benefit associated with these approaches [9].

Concurrent chemoradiotherapy (CRT) as a neoadjuvant therapy has preferable clinical efficacy and has become the standard treatment for local advanced EC with recognised guidelines [10–12]. Compared with chemotherapy or radiation alone, CRT has outstanding advantages. Not only does it achieve a higher rate of complete pathologic regression of oesophageal tumours, but it is also associated with a significant survival benefit [12]. A complete tumour response was frequently observed after neoadjuvant CRT (NCRT), and this has prompted investigations on the role of definitive concurrent chemoradiotherapy (DCRT) in locally advanced oesophageal carcinoma. However, most of those studies came from western, developed countries, and the majority of patients had adenocarcinomas. Different cell pathologies of the tumours could influence the clinical outcome following the same treatment strategy. In recent studies, neoadjuvant or adjuvant chemotherapy was associated with survival benefits in patients suffering from adenocarcinomas of the oesophagus. A prospective clinical study from Hong Kong University investigated the efficacy of CRT (three-dimensional conformal radiation therapy (3DCRT) in combination with two cycles of 5-fluorouracil (5-FU) and cisplatin) compared with surgery in oesophageal squamous cell cancer. Though this trial had shown no significant difference in the 2-year overall survival (OS) between the two study arms, a superior 5-year OS was found in the CRT arm, but with no statistical significance [13, 14].

In recent studies, both oxaliplatin and capecitabine have been shown to be at least equivalent to cisplatin and 5-FU in the treatment of advanced upper gastrointestinal (GI) cancer or EC. Also, they can be given as a convenient 2-h infusion and an oral administration, and they have a more favourable toxicity profile compared to cisplatin and 5-FU [15, 16]. Based on these previous findings, this randomised, open-label, multicentre clinical trial aims to compare outcomes in Chinese patients with locally advanced resectable oesophageal squamous cell cancer (ESCC) who have received either NCRT plus surgery or DCRT. The primary endpoints will be 2-year/5-year OS, and the secondary endpoints will be 2-year/5-year progression-free survival (PFS), treatment-related adverse events (AEs) and the patients’ quality of life (QoL). Additionally, in the subgroup analysis of CRT, we will investigate the effect and AEs between the different chemotherapy regimens: Xelox (capecitabine + oxaliplatin), PF (cisplatin + 5-FU) and single capecitabine. This is the first head-to-head clinical trial to compare CRT with radical operation in Chinese mainland people with locally advanced ESCC.

## Methods/design

### Study design

A multicentre, open, prospective, randomised controlled trial will be conducted that includes three regional hospitals in Henan, which is the area with the highest incidence of ESCC in the world, including the First Affiliated Hospital of Henan University of Science and Technology (HUST), Anyang Tumour Hospital of HUST and Nanyang Centre Hospital. A total population of 216 × 10^5^ is served by these three hospitals. The trial flow chart is shown in Fig. 1. The Standard Protocol Items: Recommendations for Interventional Trials (SPIRIT) checklist is provided in Additional file 1.

**Fig. 1 Fig1:**
[figure not shown]
Flow chart of the trial

### Ethical approval

This study protocol was approved by the Ethics Committees of the First Affiliated Hospital of HUST, Anyang Tumour Hospital of HUST and Nanyang Centre Hospital. The study is performed in accordance with the Declaration of Helsinki, and written informed consent will be collected from each study participant prior to enrolment.

### Study participants

#### Setting

The study will take place at the First Affiliated Hospital of HUST, Anyang Tumour Hospital of HUST and Nanyang Centre Hospital.

#### Patients

A total of 196 ESCC patients with T1bN + M0 or T2-4aN0-2 M0 will be randomised to the CRT group or the surgery group.

#### Inclusion criteria

The inclusion criteria are as follows:Age 18–75 yearsMainland ChineseOesophageal squamous cell cancer confirmed by histologyTumour is resectableClinical stage cT1bN + M0 or cT2-4aN0-2 M0Performance status score 0–2.

#### Exclusion criteria

The exclusion criteria include the following:Patient has distant metastasis to solid visceral organs or local invasion into the trachea, descending aorta or recurrent laryngeal nervePatient has a serious premorbid condition or a poor physical status that compromises the thoracotomyCompromised cardiac function or creatinine clearance less than 50 ml/minMaximal voluntary ventilation (MVV) of pulmonary function test is less than 30%.

#### Withdrawal criteria

Patients will be withdrawn from the study if they withdraw informed consent and decline to continue treatment or follow-up.

#### Recruitment

Recruitment will be from cancer centres of the First Affiliated Hospital of HUST, Anyang Tumour Hospital of HUST and Nanyang Centre Hospital, Henan province, China. Research staff will regularly check the inpatient - registry information system and identify any potentially eligible patients. They will liaise with an oncologist to ensure that the patient’s history and screening results are clear for study commencement. Eligible participants who present at the cancer centre when research staff are present will complete informed consent documentation after discussion with the oncologist, fill out baseline measures and then be randomly allocated to the DCRT group or the NCRT plus surgery group.

#### Randomisation

The randomisation codes will be generated by the study statistician using computer-generated random numbers. Participants will be randomly allocated to the DCRT or the NCRT plus surgery group in 1:1 order. Then in each group, participants will be secondarily randomly allocated to subgroups with one of three different chemotherapy regimens in 1:1:1 order.

#### Pretreatment investigations

Patients will receive further staging workup, including oesophagoscopy, endoscopic ultrasonography (EUS), computed tomography (CT) of the thorax and abdomen with contrast and ultrasonography of the cervical region with fine-needle aspiration cytology for any suspicious nodes. Positron emission tomography-computed tomography (PET-CT) will be used when the disease stage is difficult to confirm by general imaging examination, but it is not compulsory.

### Interventions

#### Standard oesophagectomy

Standard oesophagectomy surgery will be performed for patients by specialists. The surgical approach to the mid or lower thoracic oesophagus will be standardised to two-stage oesophagectomy to achieve a 5-cm minimum proximal margin. For tumours located over the proximal mid thoracic oesophagus where a 5-cm proximal margin cannot be achieved, a three-stage oesophagectomy will be performed. We will perform a two-field lymphadenectomy in situations of either cervical or thoracic anastomosis. All the oesophagectomies will be performed through the thoracoscopy operation or an open approach. A radical surgical resection is defined as macroscopic clearance of the oesophageal tumour with no residual disease left (R0). Patients in the standard oesophagectomy group will receive postoperative adjuvant chemotherapy if the resection is considered to be R1, i.e. microscopic disease is left behind.

#### Chemoradiotherapy

##### Radiotherapy

Intensity-modulated radiation therapy (IMRT) will be performed for patients in the DCRT group with 50 Gy/25 F and in the surgery group with 42 Gy/21 F for NCRT, at 2 Gy/day, five times/week, until disease progression or unacceptable toxicity is found. The dosage for the individual patients will be governed by the dose constraints of the normal organs. The target volume length includes 5 cm on each side of the imaged visible tumour and malignant nodes. Radiotherapy will be delivered in two consecutive phases. Phase I starts with anterior-posterior opposing portals to 30 Gy, while phase II will be given with three fields to another 20 Gy (or 12 Gy in the surgery group for NCRT), which is subject to the limiting radiation dose of the heart, lung and spinal cord.

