Researchers from Hong Kong University initiated an excellent prospective clinical trial to compare the long-term outcomes between DCRT and surgery for ESCC patients. In this study, the overall 5-year survival favours CRT, but the difference did not reach statistical significance (surgery 29.4% and CRT 50%, *p* = 0.147) [13, 14]. The intervention of chemoradiotherapy used in this study is cisplatin 60 mg/m^2^ with hydration therapy given on days 1 and 22, whereas 5-FU is administered as a continuous infusion at 200 mg/m^2^/day from day 1 to day 42. Radiotherapy was delivered as three-dimensional conformal radiation therapy (3DCRT) with a total of 50–60 Gy given in 25–30 fractions over 5–6 weeks. It is inconvenient for patients to be administered 5-FU continuously for 42 days, while IMRT has been reported as more effective and tolerable than 3DCRT. Therefore, we designed this study to investigate the role of DCRT compared with NCRT followed by radical operation in patients with locally advanced ESCC in the highest incidence area worldwide using IMRT (50 Gy/25 F) and different chemotherapy regimens (capecitabine, Xelox, PF, randomised delivery). In the pilot trial, 86 patients finished 16 weeks of follow-up with at least these three regimens in the DCRT group (capecitabine:Xelox:PF = 24:37:25) [19, 20]. The incidences of grade 3–5 AE were 25%, 32.4% and 64% (*p* = 0.03) and the pathological complete response (pCR) rates were 50%, 48.6% and 48% in the three subgroups, respectively (*p* = 0.99). Additionally, objective response rates (ORRs) of 87.5% (21/24), 83.8% (31/37) and 100% (25/25), respectively (*p* = 0.133) were observed. No differences were seen in the complete response (CR) and ORR between the three subgroups. Therefore, it is worth exploring the roles of both the DCRT and single capecitabine in CRT in patients with advanced ESCC using a larger sample size.

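### The Radiotherapy section assigns IMRT to both arms, then describes the same course as opposing portals to 30 Gy followed by three fields

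*Protocol article*

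**What the plan says.** The Radiotherapy section (Interventions, Chemoradiotherapy) opens with the technique: "Intensity-modulated radiation therapy (IMRT) will be performed for patients in the DCRT group with 50 Gy/25 F". The same sentence carries on to the other arm: "in the surgery group with 42 Gy/21 F for NCRT, at 2 Gy/day, five times/week". By that sentence, IMRT is the technique in both arms.

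Later in the same paragraph comes a description of delivery: "Radiotherapy will be delivered in two consecutive phases". The first is given as "Phase I starts with anterior-posterior opposing portals to 30 Gy". For the second, "phase II will be given with three fields to another 20 Gy (or 12 Gy in the surgery group for NCRT"), subject to the limiting doses of the heart, lung and spinal cord. No arm, centre or subset of patients is excepted, and nothing explains how the phases relate to the IMRT sentence.

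Two other places name the technique, both for DCRT. The Abstract (Methods/design) says that in the DCRT group "patients will be given intensity-modulated radiation therapy (IMRT) with 50 Gy/25 fractions"; it names no technique for the neoadjuvant treatment. The Discussion contrasts the 3DCRT of the earlier prospective trial of chemoradiotherapy against surgery with IMRT, on the ground that "IMRT has been reported as more effective and tolerable than 3DCRT", and then describes the present design as using IMRT at the DCRT dose.

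**The concern.** The two descriptions sit in one paragraph and cover the same treatment. An anterior-posterior opposing pair is, as the term is ordinarily used, a fixed-field arrangement. A centre that takes the opening sentence as the instruction would plan IMRT; a centre that takes the phase text as the instruction would treat with opposing portals and then three fields.

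Three things are at stake:

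- **Normal-organ exposure.** The section itself makes the individual dose depend on normal-organ constraints and names the heart, lung and spinal cord as limiting. Beam arrangement affects how dose reaches those organs.
- **The adverse-event endpoint.** Treatment-related adverse events are a secondary outcome. If technique differs between centres, part of the variation in toxicity would come from a factor that the plan does not acknowledge.
- **The rationale.** The Discussion gives the reported advantage of IMRT over 3DCRT as one of its reasons for a new trial. If the phase text is followed, much of the dose is not delivered by the technique which that reason invokes.

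**Working it through.** No sample-size, power or alpha formula applies. The check asks whether the two descriptions refer to the same course and, if so, how much of it the conflict covers.

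**Inputs, all from the Radiotherapy section**

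- DCRT: 50 Gy, 25 fractions, 2 Gy per day
- Neoadjuvant treatment, surgery group: 42 Gy, 21 fractions, 2 Gy per day
- Phase I: 30 Gy, anterior-posterior opposing portals
- Phase II: three fields, a further 20 Gy (DCRT) or 12 Gy (surgery group)

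**Step 1: reproduce the stated totals** (fractions × dose per fraction)

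- DCRT: 25 × 2 = 50 Gy, as stated
- Surgery group: 21 × 2 = 42 Gy, as stated

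**Step 2: add the phases** (phase I + phase II)

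- DCRT: 30 + 20 = 50 Gy
- Surgery group: 30 + 12 = 42 Gy

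At 2 Gy per fraction these are 15 + 10 = 25 fractions and 15 + 6 = 21 fractions. Totals and fraction counts match the IMRT sentence in both arms. The phase text leaves no dose over, so it cannot be an added boost. It describes how the prescribed course is to be given.

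**Step 3: share of the dose in the opposing-portal phase** (phase I ÷ total)

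- DCRT: 30/50 = 60%
- Surgery group: 30/42 = 71%

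**Step 4: compare the techniques, part by part**

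- Phase I: IMRT according to the opening sentence, opposing portals according to the phase text. This is the clear conflict.
- Phase II: IMRT according to the opening sentence, three fields according to the phase text. Three fields could in principle be intensity-modulated, but the text does not say so. This part is unclear rather than contradictory.

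**Step 5: compare with the other sections.** The Abstract and the Discussion agree with the opening sentence for DCRT. Neither mentions portals or phases, and neither states a technique for the neoadjuvant treatment. The IMRT assignment in the surgery arm therefore rests on the Radiotherapy section alone.

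**The case against.** The strongest reply is that the article is a condensed account. The Data management section refers to a separate protocol, which may give a single clear technique that the centres already follow. That limits what can be said about practice. It does not remove the point, because nothing is being called missing: the published text states two techniques for the same dose.

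A second reply is that the article never defines IMRT, so the incompatibility rests on the ordinary meaning of radiotherapy terms. This is correct, and it is why the point is confined to the opposing-portal phase.

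A third is that organ exposure is not left open, since the section applies normal-organ constraints under either reading. This stands as a mitigating feature, although the section gives no numerical limits.

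Several stronger readings are tempting, and the document does not support them:

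- **That the article calls all radiotherapy IMRT throughout.** Only the Radiotherapy section assigns it to both arms. The Abstract and the Discussion name it for the DCRT group or dose.
- **That the ambiguity is specific to the experimental treatment, or biases the survival comparison.** The same phase text covers both arms, and nothing in the document shows that it would bias overall survival.
- **That IMRT is the reason for the trial, or that its conclusion rests on IMRT.** The Discussion also cites the inconvenience of prolonged 5-FU infusion, the scarcity of head-to-head evidence, unclear long-term survival in squamous cell disease, the high-incidence setting and the choice of regimens. Its closing statement concerns DCRT and single capecitabine, not technique.
- **That the centres do treat differently.** The text permits this; the document does not show that it happens.

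**Conclusion.** The point holds as an internal contradiction in the Radiotherapy section: IMRT is assigned to both arms, and the same course is then described as starting with opposing portals. The clear conflict covers 30 Gy in each arm, which is 60% of the DCRT dose and 71% of the neoadjuvant dose.

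This rests on two assumptions: that the terms carry their ordinary meaning, and that the phase text applies to every irradiated patient, as its unrestricted wording indicates.

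The percentages are shares of dose. They are not estimates of any effect on survival or toxicity, and none can be derived from the document. Dose and fractionation are consistent, and no sample size, power or primary analysis depends on the point. The consequences are for consistency of treatment across three hospitals, normal-organ exposure, reading of the adverse-event results, and one strand of the rationale. The text is wrong as written and should be fixed, but it does not threaten the primary comparison.

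**What to change.** Reconcile the Radiotherapy section internally, and with the Abstract and the Discussion, so that one delivery technique is stated for each arm. If the phase text is meant to describe part of an IMRT plan, or to apply only in certain circumstances, the section should say so. Issue the reconciled text to all three hospitals. Which technique is right is for the investigators to settle; no view is taken here.

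Recruitment began in April 2017, so patients may already have been treated under either reading. Record the technique actually used for each patient, including those already treated, so that it can be described by arm and centre alongside the adverse-event results.

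The cost is a protocol clarification and one recorded field per patient. Sample size, randomisation and the primary analysis stay as they are.

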##### Chemotherapy

Patients will be randomised to one of following three regimens:Xelox: oxaliplatin 65 mg/m^2^, d1, 8, 22, 29, plus capecitabine, 625 mg/m^2^, bid, d1–5; 6 weeks in totalSingle capecitabine: capecitabine, 625 mg/m^2^, bid, d1–5; q1w, 6 weeks in totalPF: cisplatin, 75 mg/m^2^, d1, 29, 5-FU, 750 mg/m^2^, CIV 24 h, d1–4, d29–32.

#### Outcome measures

The primary outcome measures are 2-year/5-year overall survival (OS). The secondary outcomes are 2-year/5-year disease-free survival (DFS), treatment-related AEs and QoL. The recurrence of the disease is defined as either endoscopic recurrence confirmed with biopsy or distant metastasis. The operative mortality is defined as an in-hospital death within 30 days of the perioperative period.

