### Sample size estimation and statistical analysis

Sample size calculation is based on the 5-year OS rates: 29.4% in patients treated with oesophagectomy and 50% in the DCRT group [18]. We used the log-rank test to compare the survival rate difference between the surgery and DCRT group. We defined α as 0.05 and β as 0.2. We supposed that the rate of loss to follow-up per year is 2.5% and 12.5% in 5 years. A sample size of 96 patients was determined to be required for each group.

The primary and secondary outcome measures will be compared using Student’s *t* test for the normally distributed data and the Mann-Whitney *U* test for the nonparametric data. For the data in proportions, a chi-squared test or Fisher’s exact test (if one of the expected values is less than 5) will be used. The provision of a 95% confidence interval will be calculated with the relative risk for cancer recurrence, morbidities and mortalities related to each therapy. We will use the Kaplan-Meier curve to represent the probability of survival within 2 years and 5 years after the initial diagnosis, and compare the two groups using the log-rank test. A value of *p* < 0.05 is considered to be statistically significant. The statistical analysis will be performed with the SPSS software (version 13.0; SPSS Inc., Chicago, IL, USA).

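### 2-year and 5-year OS are both primary and unranked under one p < 0.05 threshold, with only 5-year OS sized; if either may count, type I error is about 8–9%

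*Protocol article*

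**What the plan says.** The Outcome measures section states: "The primary outcome measures are 2-year/5-year overall survival (OS". The abstract uses the plural, "The primary endpoints are 2-year/5-year overall survival", and the last paragraph of the Background repeats the pair. No section says which time point leads, or whether one or both must succeed.

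The section on sample size and statistical analysis says three relevant things:

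- **Sizing.** "Sample size calculation is based on the 5-year OS rates: 29.4% in patients treated with oesophagectomy and 50% in the DCRT group", with "We defined α as 0.05 and β as 0.2", and "We used the log-rank test to compare the survival rate difference between the surgery and DCRT group". No 2-year survival rate is assumed anywhere in the article.
- **Analysis.** The Kaplan-Meier curve is used "to represent the probability of survival within 2 years and 5 years after the initial diagnosis, and compare the two groups using the log-rank test". The same section assigns data in proportions to a chi-squared or Fisher's exact test, which could be applied to 2-year and 5-year survival rates.
- **Threshold.** A p-value below 0.05 "is considered to be statistically significant". This is one threshold, with no distinction between the two time points.

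**The concern.** Two primary time points on the same survival curve give two chances of a positive trial if each is tested at 0.05 and either suffices. A 2-year p of 0.04 could be reported as a positive primary result, and so could a 5-year p of 0.04 after a null result at 2 years. The stated α of 0.05 would then no longer describe the trial's error rate.

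The sizing adds to the problem. The whole α was given to the 5-year comparison, so none was reserved for 2 years, and the 2-year comparison has no power statement of its own. This matters because the trial asks whether a non-surgical strategy improves on what the abstract calls the gold standard. A claim of that kind should not depend on which of two time points happened to cross 0.05.

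**Working it through.** **Inputs from the article.** 5-year OS 29.4% v 50%; α 0.05 (sidedness not stated); power 80%; loss 12.5% over 5 years; 96 per group required; 196 to be randomised 1:1, so 98 per arm.

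**1. The plan's own figure.**
- Hazard ratio = ln(0.50)/ln(0.294) = 0.566.
- Schoenfeld events at two-sided 0.05 and 80% power: 4 × (1.960 + 0.842)² / (ln 0.566)², rounded up to 98.
- Mean 5-year event probability = 1 − (0.294 + 0.50)/2 = 0.603. Per arm: 98/(2 × 0.603) = 81.3, so 82. After loss: 82/0.875 = 93.7, so 94.
- The exponential log-rank formula (Lachin) gives 83.8 per arm, and 83.8/0.875 = 95.8, so 96.

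The stated 96 is therefore reproduced by a two-sided log-rank calculation on the 5-year rates with the full 0.05. The one-sided versions tried give 74–91 and do not reproduce it.

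**2. Type I error if both time points are tested and either counts.** Assume exponential survival and no treatment effect, so that 2-year OS = (5-year OS)^0.4. For two log-rank tests on the same curve, correlation = √[(1 − S2)/(1 − S5)]. For two comparisons of survival proportions, correlation = √[(1 − S2)·S5 / ((1 − S5)·S2)]. Overall error = 1 − P(|Z2| ≤ 1.96 and |Z5| ≤ 1.96) under a bivariate normal.

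| Null 5-year OS | 2-year OS | Log-rank: correlation, error | Proportions: correlation, error |
|---|---|---|---|
| 29.4% | 61.3% | 0.741, 8.1% | 0.513, 9.0% |
| 39.7% | 69.1% | 0.716, 8.3% | 0.543, 8.9% |
| 50% | 75.8% | 0.696, 8.4% | 0.565, 8.9% |

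A simulation of 20,000 null trials (98 per arm, 5-year OS 39.7%, log-rank) gave 5.0% at 2 years alone, 4.9% at 5 years alone and 8.1% for either. Independent tests would give 1 − 0.95² = 9.75%, which is a ceiling.

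**3. Power at 2 years.** With constant hazards, the design rates imply 2-year OS of 0.294^0.4 = 61.3% v 0.50^0.4 = 75.8%. Expected deaths by 2 years = n × (0.387 + 0.242). Power = Φ(√d/2 × |ln 0.566| − 1.96).

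| Per arm | Deaths by 2 years | Log-rank power at 2 years |
|---|---|---|
| 84 (96 × 0.875) | 52.9 | 54% |
| 96 | 60.4 | 60% |
| 98 | 61.7 | 61% |

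The row for 84 is a harsh lower end, because it removes all five years' loss by year 2. At 5 years the same formula gives 86% with 96 per arm and 82% with 84. For 80% power at 2 years, about 156 per arm (log-rank) to 160 (proportions) would be needed before allowing for loss.

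**4. What an alpha split would cost.** At 0.025 for each time point, the 5-year comparison needs 118 events (Schoenfeld). That is 118/1.206 = 97.8 per arm, and 97.8/0.875 = 111.8, so about 112 against the stated 96. Sizing at the full 0.05 is not compatible with a split.

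**The case against.** The strongest reply is that the article never says two separate tests will be run. It describes one Kaplan-Meier curve and names the log-rank test in the singular. A fair reading is one test over all follow-up, with 2-year and 5-year survival read off the curve, and then there is no inflation. Likewise, if both time points had to be significant, the error would be at most 5%. Both replies stand, so the 8–9% can only be conditional. They do not remove the ambiguity: on the single-test reading, the Outcome measures section misdescribes the primary endpoint. On the both-must-succeed reading, joint power cannot exceed the roughly 60% available at 2 years.

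A second reply is that this is a condensed article and that endpoint hierarchy is often left to the analysis plan. This also stands as far as it goes: the absence of an alpha rule is not itself the point. The point is what the article does fix, namely two unranked primary endpoints, one threshold and the full α in the sizing. A later split would undercut that sizing.

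A third reply is that sizing on 5-year OS suggests it is the confirmatory target. That is plausible, but no section says so.

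Some stronger readings are tempting but unsupported:

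- A reader might infer that the 2-year comparison is an unadjusted interim look. No section schedules a 2-year efficacy analysis ahead of the 5-year one, or early stopping on OS; both could be reported once, at the end.
- A reader might use the Hong Kong precedent, which found "no significant difference in the 2-year overall survival (OS) between the two study arms", to argue that 2-year OS is misplaced. That trial's 5-year difference was also non-significant (p = 0.147, Discussion), so it does not single out 2 years.
- The 2-year power is illustrative. Perioperative mortality of about 5%, cited in the Background, makes constant, proportional hazards doubtful here. Lower power at an earlier point on the same curve is expected and does not weaken the 5-year test.

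**Conclusion.** The point holds in conditional form. The article names two primary time points without ranking them, sets one 0.05 threshold and sizes only the 5-year comparison at the full α. Following the text, either could be claimed as a primary success.

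If each is tested and either counts, overall type I error is about 8.1–8.4% (log-rank) or about 9% (proportions), given exponential survival. It would be wrong to state that the trial's false-positive rate is 8%, because the article fixes neither two tests nor an either-counts rule. Log-rank power at 2 years is about 54–61% under the plan's own hazard ratio with constant hazards, against the stated 80%. What needs no assumption is that the confirmatory endpoint is not identified and that 2-year OS was not sized.

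**What to change.** In the abstract, the Background, Outcome measures and the statistical section, name one confirmatory primary analysis: OS compared once between the arms by log-rank over the 5-year follow-up, at two-sided 0.05.

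For 2-year OS, choose one of two options and state it:

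- report it as a secondary Kaplan-Meier estimate per arm, with the difference and its 95% confidence interval and no significance claim; or
- test it in fixed order, only if the 5-year OS test is significant.

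Either option keeps α at 0.05 and the planned 96 per group. The change is wording only and should be made before outcome data are examined. The cost is that no stand-alone primary claim can be made at 2 years; under the fixed-order option, a 2-year claim remains possible after a significant 5-year result.
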